#### Drop-out criteria

Women with complications during pregnancy as assessed by participating obstetricians and physicians will be excluded from the study. Furthermore, women who will give birth pre-term (delivery before 37th week of gestation), who will not have participated regularly in the program (less then 80% of the units) or who will have missed blood tests (at the beginning of the program or 36th week of gestation) will be excluded.

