#### Secondary outcomes

Secondary outcomes will be assessed during pregnancy and postpartum and will include:
The course of pregnancy (weight gain according to the recommendations of the Institute of Medicine (IOM) [45], manifestation of pregnancy-induced diseases, mode of delivery)Anthropometric data of the mother and the father (weight, height, BMI, circumferences, body fat distribution)Anthropometric data and health status of the new-born (birthweight, length, head circumference, umbilical artery pH value, Apgar scores at one, five and ten minutes)Cord blood biomarkers in the newborn (insulin, leptin, adiponectin, resistin, BDNF, TNF-α, IL-6, CRP, fetuin A)Maternal and paternal biomarkers (insulin, leptin, adiponectin, resistin, BDNF, TNF-α, IL-6, CRP, fetuin A) during and after pregnancyMaternal cortisol level in the saliva at mid-pregnancyPostnatal depression (using the Edinburgh Depression Scale) 8 weeks after birthInfant development (age-appropriate development of fine and gross motor skills, communication, personal and social skills)

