#### Statistics

The main variable (BMI at 24 months) will be analyzed by covariance analyses evaluated by the factor group, breastfeeding, and smoking as well as covariances of parental age, paternal BMI, socioeconomic status, breastfeeding, and potential pregnancy-induced diseases (e.g. gestational diabetes mellitus, pregnancy-induced hypertension (PIH)). The significance level alpha will be set at < 0.05 for all analyses. All confidence intervals will be estimated at 95%. Missing data will be calculated according to the LVCF approach (Last Value Carried Forward). Analyses will be carried out as per-protocol-analyzes and intention-to-treat analyses (ITT). Spearman and Pearson correlation procedure will be used to assess relationships between maternal data (physical activity in METs, eating habits, weight gain, blood samples) and neonatal data (birth weight, length, head circumference, Apgar scores, cord blood sample) as well as infants’ development. Multiple linear regressions will be performed for neonatal measures to determine correlations with maternal and paternal lifestyle factors. The model will include group (intervention yes/no) as well as maternal and paternal characteristics as possible confounders. Explained variance (r-squared) for the linear regression model will be reported as model fit statistic.

Statistical analysis will be performed using SPSS 24.0 data-analysis software (Statistical Product and Service Solutions 24.0) and data analysis will be blinded.

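### The drop-out criteria exclude women for mostly post-randomisation events without limiting this to a per-protocol set, which conflicts with the promised ITT analysis and a listed secondary outcome

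*Protocol article*

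**What the plan says.** The Drop-out criteria section (under Participants) has two operative sentences. The first reads "Women with complications during pregnancy as assessed by participating obstetricians and physicians will be excluded from the study". The second adds "women who will give birth pre-term (delivery before 37th week of gestation" and women "who will not have participated regularly in the program (less then 80% of the units) or who will have missed blood tests"; the tests meant are those at programme start and at week 36. Only the first sentence names the study as what these women leave; the second says simply that they will be excluded. Neither mentions an analysis set.

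Three other places bear on this:

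- **Statistics**, on analysis sets and missing data: "Analyses will be carried out as per-protocol-analyzes and intention-to-treat analyses (ITT" and "Missing data will be calculated according to the LVCF approach (Last Value Carried Forward".
- **Secondary outcomes**: the course of pregnancy includes "manifestation of pregnancy-induced diseases, mode of delivery".
- **Statistics**, on the model for 24-month BMI: its covariates include "potential pregnancy-induced diseases (e.g. gestational diabetes mellitus, pregnancy-induced hypertension (PIH".

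The primary outcome is the infant's BMI at two years. The Follow-up section takes infant weight and height from examination records at 1, 4, 8, 12 and 24 months.

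**The concern.** An ITT analysis compares everyone randomised, in the arm to which they were randomised. A rule that drops women for poor attendance, for complications or for early delivery removes them because of things that happened after allocation. If their infants are then not measured at 24 months, the comparison is between those who remain in each arm.

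Attendance, complications and preterm birth may each depend on the arm, since the intervention is meant to change the course of pregnancy. They may also relate to child BMI; the protocol's own Background links gestational diabetes to later obesity in the child. Selecting on such variables removes the protection of randomisation for the primary endpoint. A missed maternal blood test adds a further loss: it removes an infant whose BMI could still have been recorded.

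The same rule may take out cases of a listed secondary outcome, and of the covariates in the primary model.

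**Working it through.** **1. Criteria against the promised analyses.**

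| Criterion | When it arises | Consequence if applied as written |
|---|---|---|
| Complications in pregnancy | During pregnancy | No infant BMI unless follow-up continues; cases of the secondary outcome may be lost |
| Delivery before week 37 | At birth | At most birth values exist; newborn outcomes are truncated |
| Under 80% of units | During the programme | Selection on adherence |
| Missed blood test, programme start or week 36 | Week 36 falls within the programme; the first test may precede allocation | Loss for a reason unrelated to the endpoint |

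The text does not state when randomisation takes place, and the pre-programme sample is at week 8. So the first blood test cannot be placed after randomisation with certainty; the remaining events can.

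**2. Does the missing-data rule repair it?** No. A woman dropped during pregnancy has no infant measurement to carry forward. An infant excluded at preterm birth has at most birth weight and length, which do not stand in for a 24-month BMI. No section says that excluded pairs stay in follow-up.

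**3. How the plan budgets drop-outs.** The Sample size section goes from 48 to 60 for 25% drop-out: 48 × 1.25 = 60. Removing 25% of 60 leaves 60 × 0.75 = 45. Either way, drop-outs are treated as lost; there is no category for women who leave the programme but remain in follow-up. (The derivation of 48 is a separate matter and is not used here.)

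**4. How strict the attendance rule is.** Twice weekly over weeks 13 to 36 (24 weeks) is 24 × 2 = 48 exercise sessions. 80% of 48 is 38.4. Missing 10 leaves 38/48 = 79.2%, which fails on exercise units alone. The control activity is one relaxation class a week.

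**5. Size of bias, by assumption.** Let a share p of an arm be excluded, and let excluded infants differ from retained ones by D. Then overall mean = (1 − p) × retained mean + p × (retained mean + D), so the retained mean is off by p × D. With the same D in both arms, the bias in the difference is (p₁ − p₂) × D.

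- Assumed p₁ = 0.30 (intervention), p₂ = 0.10 (control), D = 0.5 kg/m²: 0.20 × 0.5 = 0.10 kg/m².
- Same p, D = 1.0 kg/m²: 0.20 × 1.0 = 0.20 kg/m².

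That is 10% to 20% of the 1 kg/m² target. None of p₁, p₂ or D comes from the documents.

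A second illustration assumes no true effect and that only the intervention arm loses its least adherent share r. With correlation ρ between adherence and infant BMI, the spurious difference is ρ × φ(z_r)/(1 − r) in SD units. For r = 20% and ρ = 0.1 it is 0.035; for r = 40% and ρ = 0.5 it is 0.322. The range is about 0.04 to 0.32 SD.

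**6. Power.** At the stated effect size of 1.0 (two-sided t-test, α = 0.05), power is 96.8% with all 60 women, 90.6% with 45 and about 75% with 30. Unless losses are very large, the harm is mainly bias rather than lost power.

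**The case against.** The best defence is that the section is a per-protocol definition under a poor heading. Promising both per-protocol and ITT analyses only makes sense if the two sets differ, and a carry-forward rule presupposes that some participants with incomplete data stay in an analysis. Only the complications sentence explicitly says that women leave the study. This weakens any claim about intent, but it does not remove the conflict: no section limits the criteria to a per-protocol set or keeps excluded pairs in follow-up.

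A reader might infer several stronger things that the document does not support:

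- **That ITT is impossible, or that the ITT set equals the per-protocol set.** This follows only from the literal reading.
- **That all four criteria arise after randomisation.** The first blood test may not.
- **That the pregnancy-disease comparison is emptied of events.** Complications are left to physicians' assessment, a diagnosis could be recorded before exclusion, and keeping gestational diabetes and PIH as covariates suggests that some such women are expected to remain. Cases may be depleted, by an unknown amount.
- **That the 80% rule certainly applies to both arms.** This is unstated. If it covers controls, it acts on a much lighter schedule; if it does not, only the intervention arm is selected. It selects differently by arm either way.
- **That not naming a primary set is itself an error.** A protocol article may leave that to the full protocol or analysis plan.

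The illustrated bias is also modest. With the SD of 1 kg/m² implied by a 1 kg/m² difference at effect size 1.0, and 30 per arm, the standard error of the difference is √(2/30) = 0.26, so 0.10 to 0.20 kg/m² lies below one standard error. The figures do not carry the point; the contradiction in the text does.

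**Conclusion.** The concern stands as a conflict in the text. The Drop-out criteria section states exclusions that are not confined to a per-protocol set. Read as written, they conflict with the ITT analysis, with pregnancy-induced diseases as a secondary outcome, and with gestational diabetes and PIH as covariates. The carry-forward rule does not resolve this.

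The consequence for the primary endpoint is exposure to selection bias of unknown size and direction. The 0.10 to 0.20 kg/m² figure rests wholly on assumed exclusion rates and an assumed difference between excluded and retained infants. Confidence is high that the passages conflict; how much bias results, and how many disease cases are lost, cannot be determined from the document. It should be corrected because it affects the primary comparison, and because an analysis plan cannot recover 24-month measurements that were not collected.

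**What to change.** Reconcile the Drop-out criteria section with Secondary outcomes and Statistics:

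1. State that the listed criteria define exclusion from the per-protocol set only, and say whether the 80% rule applies to controls.
2. Separate stopping the programme from leaving follow-up. Obtain 24-month BMI for every randomised mother-infant pair, whatever the attendance, blood tests, complications or gestational age at birth.
3. In Statistics, say that the ITT analysis includes all randomised pairs in their allocated arm, preferably with per-protocol as supportive.
4. Count pregnancy-induced diseases in all randomised women.

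Clinical decisions to stop exercise are unaffected. The cost is a wording change plus some extra contact with women who would otherwise be dropped. Infant weight and height already come from examination records, so the added measurement burden is small.

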#### Sample size

Power analysis was done based on recommendations of weight gain in German children at 24 months after birth [37]. Normal weight gain (50th percentile) after subtraction of birth weight is nine kilograms at the age of 24 months. The BMI shows a difference of 1 kg/m^2^ at this time point (50th percentile). Therefore, a difference of 1 kg/m^2^ at the age of two years between the intervention and the control group will be assumed. To detect this difference in proportions with 80% power (GPower analysis) using a significance level of 0.05 and an effect size of 1.0, 48 women are needed. Calculating with a drop-out rate of 25% during the program, 60 women are required and planned to be recruited for this study.

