**Methods/design:**

A randomized multi-center controlled trial will be conducted in Germany, comparing supervised aerobic and resistance training 2x/week (13th to 36th weeks of gestation) and nutritional counseling (6th to 36th weeks of gestation) during pregnancy with usual care. Thirty women (pre-pregnancy Body Mass Index ≥25 kg/m^2^, 6th–10th week of gestation) will be included in each group. Maternal anthropometric and physical measurements as well as blood sampling will occur at the 6th–10th, 13th–14th, 21st-24th, and 36th week of gestation, at delivery as well as 8 weeks and 24 months postpartum. Neonatal measurements and umbilical blood sampling will be performed at birth. Maternal and infants’ weight development will be assessed every 6 months till 24 months postpartum. A difference in childhood BMI of 1 kg/m^2^ at the age of two years between both groups will be assumed. A power size of 80% using a significance level of 0.05 and an effect size of 1.0 is presumed.

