#### Primary outcome

The primary outcome of this study will be the BMI of the infant at two years after birth assessed by German percentile [44].

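### The 48 women in the sample size statement cannot be reproduced from its stated inputs: effect size 1.0, 80% power and two-sided alpha 0.05 give 34

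*Protocol article*

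**What the plan says.** The Sample size section sets the target in BMI units: "a difference of 1 kg/m^2^ at the age of two years between the intervention and the control group will be assumed". The next sentence turns this into a power statement. It opens "To detect this difference in proportions with 80% power (GPower analysis" and ends "using a significance level of 0.05 and an effect size of 1.0, 48 women are needed". A drop-out rate of 25% is then applied to reach 60 recruits.

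The Methods/design part of the abstract repeats three of the inputs: "A power size of 80% using a significance level of 0.05 and an effect size of 1.0 is presumed". It gives thirty women per group but not the figure 48.

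The outcome and analysis are described as continuous. Under Primary outcome: "The primary outcome of this study will be the BMI of the infant at two years after birth assessed by German percentile". Under Statistics: "The main variable (BMI at 24 months) will be analyzed by covariance analyses". Statistics also gives the alpha level, without sidedness: "The significance level alpha will be set at < 0.05 for all analyses". Allocation is 1:1, in blocks of six split 3:3 (Study design and setting). The article gives no SD for BMI at 24 months, and the power statement names neither the test nor the type of effect size.

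**The concern.** Size, power, alpha and effect size are tied by one equation, so any three fix the fourth. The article prints all four, and for a two-group comparison of means they do not satisfy it. Two further features make the intended calculation hard to recover:

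- The target is a mean difference of 1 kg/m², but the power sentence calls it a difference in proportions. The primary outcome is not binary.
- A raw difference of 1 kg/m² and an effect size of 1.0 agree only if the SD is exactly 1.0 kg/m². The figure of 48 at 80% power points to a larger SD.

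This is the article's only statement of what the trial can detect. As printed, a reader cannot tell whether the design has about 92% power for a standardised difference of 1.0 or 80% power for about 0.83. These rest on different assumptions about the spread of the primary outcome.

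**Working it through.** **Inputs.** Effect size 1.0, power 80%, alpha 0.05, 48 women, difference 1 kg/m², drop-out 25%, 60 recruited (all from Sample size); allocation 1:1 (Study design and setting). Assumptions: the effect size is Cohen's d, because the outcome is BMI; the test is two-sided, with one-sided also tried.

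**Step 1: try to reproduce 48.** The normal approximation per arm is n = 2(z_{1−α/2} + z_{0.80})²/d².

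- Two-sided: 2 × (1.960 + 0.842)²/1.0² = 15.7, so 16 per arm, 32 in total.
- With the noncentral t distribution: 16.7, so **17 per arm, 34 in total** (power 80.7%).
- One-sided, noncentral t: 13.1, so 14 per arm, 28 in total. This is further from 48.

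The stated 48 is not reproduced.

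**Step 2: try other readings with the same inputs.**

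| Reading | Total needed |
|---|---|
| Mann-Whitney test | 36 to 40 |
| ANCOVA, 1-df group effect, f = 0.5, 0 to 10 covariates | 34 to 35 |
| Effect size read as f = 1.0 | 11 |
| Two proportions, Cohen's h = 1.0, arcsine | 32 |
| Two proportions, h = 1.0, Fisher exact, assumed base rates 2% to 50% | 38 to 42 |
| Two proportions, h = 1.0, continuity-corrected, assumed base rates 2%, 3%, 4%, 5% | 52, 50, 48, 46 |
| F-test with f = 0.5, 3 numerator df, 4 groups | 48 (power 80.3%) |

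Only the last two rows reach 48. The article states neither set-up.

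**Step 3: what 48 women would give.** With 24 per arm the noncentrality is d√(24/2) = 3.464d, on 46 df.

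- Power for d = 1.0: 92.4%.
- Effect detectable with 80% power: d = 0.826. For a difference of 1 kg/m² the SD is then 1/0.826 = 1.21 kg/m².
- For comparison, 90% power for d = 1.0 needs 46 in total.

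**Step 4: what the planned recruitment leaves.** The article's 60 equals 48 × 1.25. A 25% loss from 60 leaves 60 × 0.75 = 45, not 48; keeping 48 would take 48/0.75 = 64. With 45 completers (22 and 23), two-sided alpha 0.05 and a true difference of 1 kg/m²:

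| Assumed SD (kg/m²) | d = 1/SD | Power, 48 women | Power, 45 women |
|---|---|---|---|
| 1.0 | 1.00 | 92% | 91% |
| 1.2 | 0.83 | 81% | 78% |
| 1.4 | 0.71 | 68% | 65% |
| 1.6 | 0.63 | 56% | 54% |

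At d = 0.826 exactly, 45 completers give 77.3%. The SDs above 1.0 are assumptions that show the range; the article gives none.

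**The case against.** The strongest reply is that the text is imprecise and the power need not be wrong. The power sentence names no test, and there are routes to 48. A continuity-corrected comparison of proportions gets there at a base rate near 4%. An F-test with 3 numerator df and four groups needs exactly 48, and Statistics does list three factors (group, breastfeeding, smoking). Alternatively, "an effect size of 1.0" may loosely restate the 1 kg/m² difference; with an SD of about 1.21, 48 women and 80% power then agree, and the SD may stand in the full protocol.

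This stands in part. It rules out any claim that a proportions calculation can never give 48, and it means the article does not show which element is at fault. It does not make the printed statement right. The base rate is stated nowhere and the outcome is not binary. The F-test set-up is not described, and for the 1-df group contrast the answer remains 34. If the SD was 1.21, the effect size should have been printed as 0.83. The point is therefore not the absence of an SD, which a condensed article may leave out; the printed figures conflict.

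Two other replies stand. The planned 95% confidence intervals, more than the planning power, will show what a null result excludes, so the harm to interpretation is limited. The abstract does not print 48, so it repeats the inputs but not the mismatch.

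**Conclusion.** The point holds as a correction of a stated figure. For a two-group comparison of mean BMI with d = 1.0, two-sided alpha 0.05 and 80% power, the requirement is 34 women (28 one-sided), against 48 printed. At 48, either power for d = 1.0 is about 92%, or the effect detectable with 80% power is about 0.83. This rests on reading the effect size as Cohen's d and on 1:1 allocation. Calling the target a difference in proportions contradicts the article's own outcome and analysis sections.

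A reader might infer more: that the trial is underpowered, or that the stated power or the detectable effect has been shown to be the wrong element. The article supports neither. On its printed inputs 48 exceeds 34, and even 45 completers give about 91% power for d = 1.0. Power falls below 80% only if the SD is larger than the 1.0 kg/m² implied by the text (78% at an assumed 1.2 with 45 completers), and the article does not say what SD was used. Nor does it follow that 34 is the right size for this trial, since the size, the power or the effect size could each be the misprinted element.

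**What to change.** In Sample size:

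- Remove the reference to proportions and describe a two-sample comparison of mean BMI at 24 months.
- Recover from the GPower record the SD, test and sidedness actually entered, and state them. The sponsor should report what was used and not choose a set afterwards because it fits.
- Restate one consistent set of figures, based on the 45 completers that 60 recruits and 25% drop-out leave. If the SD was 1.0 kg/m², that is about 91% power for 1 kg/m². If it was 1.2, 1.4 or 1.6, it is about 78%, 65% or 54%.

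Carry the same inputs into the Methods/design part of the abstract.

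The cost is wording only; recruitment stays at 60. The downside is that the stated power may become slightly less favourable than 80%: if the 48 came from an SD of about 1.21, 45 completers give about 77%.

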## Methods/design

### Study design and setting

The ADEBAR study is a multi-centre, two-arm, randomized controlled trial (intervention versus control group) with the primary purpose of prevention. The program will take place at three hospitals in the Rhine region (Cologne, Düsseldorf, and Bonn) in Germany. The intervention period will last approximately 30–32 weeks (8 months) depending on the date of delivery. Mothers, fathers, and their offspring are being followed until the infant is two years of age. A schematic timeline and SPIRIT timetable of the study is presented in Fig. 1 and Fig. 2.

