**Fig. 2 Fig2:**
[figure not shown]
Schedule of enrolment, interventions, and assessments

We will perform a block randomization with a block size of six including an equal number of participants for all groups within each block (3:3). This ratio was chosen as it is expected to reduce bias and allocate participants evenly between the intervention and the control group [34].

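### Sixty women do not leave 48 after a 25% drop-out (they leave 45; 48 would need 64), and the allowance stops at the end of the programme although the primary outcome is read two years after birth

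*Protocol article*

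**What the plan says.** The Sample size section of the protocol article gives the base requirement as "using a significance level of 0.05 and an effect size of 1.0, 48 women are needed", with 80% power. It then adds the allowance for loss: "Calculating with a drop-out rate of 25% during the program, 60 women are required and planned to be recruited for this study". The Intervention and Control group sections each plan for 30 participants, and the Abstract gives 30 per group, so 60 is the working target.

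On timing, Study design and setting says: "The intervention period will last approximately 30–32 weeks (8 months) depending on the date of delivery". The last scheduled contact that could count as part of the programme is a group dietary session 8 weeks postpartum (Nutrition counseling). The Primary outcome section names the "BMI of the infant at two years after birth". The Drop-out criteria section lists pregnancy complications, preterm delivery, low attendance and missed blood tests at the start or in week 36. None of these concerns loss of the child after birth.

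**The concern.** Two steps in the allowance for loss look wrong.

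- **The inflation.** Multiplying the evaluable number by one plus the drop-out rate is a familiar slip. A rate of 25% means that a quarter of those recruited are lost, so the evaluable number has to be divided by the fraction retained.
- **The period.** The rate is tied to the programme, which ends around delivery or at the latest 8 weeks afterwards. The outcome that the sample size serves is measured when the child is two. A family that completes the programme but supplies no 24-month BMI is not counted anywhere in the calculation.

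At stake is whether the number recruited yields the number that the protocol says it needs for its primary comparison, and whether readers can rely on the stated margin for loss.

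**Working it through.** **Inputs from the protocol.** Evaluable number 48, drop-out 25% during the programme, recruitment 60, significance level 0.05, power 80%, effect size 1.0 (all from Sample size); equal allocation (randomisation paragraph under Fig. 2); outcome at two years (Primary outcome).

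**Assumptions.** The effect size is Cohen's d, the test is a two-sided two-sample t-test, and a further 10–20% are lost between programme end and 24 months. The protocol gives no figure for that later loss.

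**1. Reproducing the 60.**
- N × (1 + rate) = 48 × 1.25 = 60. This matches the protocol exactly.
- N / (1 − rate) = 48 / 0.75 = 64. This is the number that leaves 48 after 25% loss.

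**2. What 60 delivers.**
- 60 × 0.75 = 45, which is 3 short of 48.
- 1 − 48/60 = 20%, the largest total loss at which 60 still leaves 48.

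**3. The uncovered period.** Counted from delivery, 24 months are uncovered. Counted from the 8-week postpartum session (about 2 months), about 22 months are uncovered. With the assumed further loss:
- 10%: 45 × 0.90 = 40.5 remain.
- 20%: 45 × 0.80 = 36 remain.

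**4. Power at these numbers.** The second effect size is the d that 48 women detect with 80% power, obtained by solving the t-test backwards. It is not a figure in the protocol.

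| Evaluable total | Power at d = 1.0 (stated) | Power at d = 0.826 (back-calculated) |
|---|---|---|
| 48 | 92% | 80% |
| 45 | 91% | 77% |
| 40.5 | 87% | 73% |
| 36 | 83% | 67% |

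The second column is needed because 48 does not follow from the stated inputs under these assumptions. At d = 1.0 and 80% power, the two-sided t-test needs 17 per arm, or 34 in total.

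**The case against.** The strongest reply is that nothing of consequence is lost. At the effect size the protocol states, 34 evaluable women suffice for 80% power, so 45, or even 36, still clears the target. A reader might infer from the shortfall that the trial is underpowered by its own assumptions. The document does not support that. The figures below 80% appear only at d = 0.826, which is inferred from 48. The mismatch between 48 and an effect size of 1.0 is a separate question about the base calculation. The lowest of those figures, 67–73%, also depend on a later loss that the protocol does not quantify. This part of the objection stands, and it limits the consequence to the evaluable number. Even at d = 0.826 the inflation slip alone costs only about 3 percentage points (80% to 77%).

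Two further points soften the follow-up gap without closing it. Infant measurements come from examination records (Follow-up), which may make 24-month values easier to obtain than a study visit would. The Statistics section plans intention-to-treat analyses with the last value carried forward, so children without a 24-month value may stay in the analysed set. But a carried-forward BMI from an earlier age is not the outcome at two years, and neither provision enters the sample-size reasoning.

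The reply does not make the text correct. The protocol does not claim that 34 are enough, nor that 48 contains a reserve. It says that 48 are needed, and its own drop-out rate leaves 45. The apparent reserve also depends on a standard deviation of 1 kg/m², which the protocol does not state.

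**Conclusion.** The last step of the sample-size section is wrong as written. With 25% loss, 60 recruited leave 45 evaluable, not 48; 48 would need 64. The 25% is also tied to the wrong interval for a two-year outcome, leaving about 22 to 24 months without any allowance. Both conclusions rest on the protocol's figures alone.

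The consequence is that the stated evaluable number is not delivered. It is not shown that the stated power is lost: at the stated effect size, with the reading given above, power stays between 83% and 91% across 36 to 45 evaluable. It falls below 80% only if the true standardised effect is nearer the back-calculated 0.826. The correction should be made because the trial relies on this figure, but the shortfall is modest and the design need not change.

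**What to change.** Keep recruitment at 60 and correct the Sample size section as follows:

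- State that 60 recruited leave 45 evaluable at 25% loss, or 48 only if total loss from randomisation to month 24 is at most 20%.
- Define drop-out, for the sample size, as having no observed 24-month BMI, so that the allowance covers the whole period up to the primary outcome.
- Restate the power for 45 and for the number expected after two-year loss, showing the assumed effect size beside each figure and giving the expected later loss as an explicit assumption.

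The cost is a change of wording. No participants are added, and the outcome and analysis are unchanged. The one drawback is that the stated evaluable number becomes slightly less favourable.
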